#### 1.4.0 Objectives and Hypotheses

In summary, TBS has been shown to be effective in open-label studies of major depression. It has also been shown to have greater potency than conventional protocols in studies of motor physiology. However, to date there has been no direct comparison of the relative efficacy of these different forms of rTMS for TRLLD under randomized controlled conditions. This study will address the question of the relative efficacy of conventional versus theta-burst stimulation in the setting of TRLLD by comparing conventional HFL rTMS to TBS, while training and validating classifier algorithms for predicting treatment response using rs-fMRI.

[figure not shown]

**Objective 1:** To compare the effectiveness of a course of 4 minute sessions of TBS to a course of 45 minute sessions of conventional rTMS in LLD.

**Hypothesis 1:** Sequential bilateral forms of TBS will have non-inferior effectiveness compared to sequential bilateral conventional rTMS in older adults with depression.

**Objective 2:** To determine if an automated classifier can use pre-treatment resting-state fMRI, clinical and cognitive data to predict treatment outcome for both TBS and conventional rTMS.

**Hypothesis 2:** Patterns from whole-brain functional connectivity, obtained from pre-treatment rs-fMRI, will distinguish responders and nonresponders with >85% accuracy for TBS and standard rTMS.

**Exploratory Objective 1:** To compare network connectivity in depressed adults across the lifespan and rTMS-induced changes between bilateral and unilateral stimulation approaches using existing unilateral data in adults <60 from our group.

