## 3.0 RESEARCH DESIGN AND METHODS

### 3.1.1 Research Design and Methods

Up to 220 outpatients at the University Health Network and the Centre for Addiction and Mental Health, meeting diagnostic criteria for unipolar major depressive disorder, will be randomized to receive conventional 1 Hz rTMS to the right DLPFC followed by 10Hz rTMS to the left DLPFC, or continuous theta-burst stimulation (cTBS) to the right DLPFC followed by left DLPFC intermittent theta-burst stimulation (iTBS), with rs-fMRI obtained before and after treatment. We have chosen a non-inferiority study design to align with the hypothesis of the study that TBS will be no different in terms of clinical outcome but faster and more efficient.

[figure not shown]

Following randomization, patients will undergo a series of clinical and cognitive assessments as well as an MRI (60 minute) and motor threshold testing to determine the appropriate site and strength of stimulation according to standard methods, and then begin treatment. If a participant is able to have an MRI but cannot tolerate the MRI, e.g. due to claustrophobia, they will still be allowed to undergo treatment using an approximated method called beam F3. This method targets the exact same neuronavigated target and has been shown to be within 3 millimeters of the neuronavigated site. The treatment phase will last between four and six weeks. Treatment will be administered daily, 5 days per week (i.e., 20-30 treatments). Participants will be permitted to miss scheduled treatment days due to illness or scheduling conflicts. They will still receive the entire 20-30 treatments, but over a longer time period (i.e. greater than 4-6 weeks). However, those who miss more than 3 consecutive treatment days will be excluded from the study as it is our intention to encourage the commitment of the participants in the study as well as discourage prolonged duration of time taken to complete the protocol as it could affect the efficacy of the treatment. All missed treatment days will be recorded in a log for each participant.

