Depressive symptoms will be assessed using the clinician-rated Montgomery Asberg Depression Rating Scale (MADRS), the 17-Item Hamilton Depression Rating Scale (HRSD-17), and the self-rated 16-item Quick Inventory of Depressive Symptoms (QIDS16). Change in scores on the MADRS, from baseline to endpoint, will be the primary clinical outcome of interest. The primary neuroimaging outcome measure will be the whole-brain functional connectivity on rs-fMRI. If the subject experiences an improvement in their symptoms by a minimum of 30% based on the change in MADRS score from baseline to week 4, they will receive an additional 10 treatments over the course of 2 weeks in an attempt to optimize treatment response. Those subjects that do not achieve a 30% reduction by week 4 will be given the opportunity to continue for 2 more weeks as they may be late responders and benefit from the additional 10 treatments. All participants will undergo a post-treatment MRI scan after they complete treatment. Participants who are in remission at weeks 3 and 4 will exit the study at week 4 and undergo a post-treatment MRI scan. For participants who do not wish to continue past week 4 they will undergo a post-treatment MRI scan (30 minutes) and complete all final visit measures.

An independent, trained rater at each site will administer the clinical assessment scales at baseline, after each 5 sessions of treatment, and at 1, 4, and 12 weeks post-treatment. Cognitive assessments will be administered at baseline, after the final treatment session (including at drop-out), and at 12 weeks following the final treatment. These assessments can be done within 1-2 days of the scheduled time point. The independent raters will be blinded to the treatment being administered. All treatments will be conducted with minimization of personal contact (i.e., verbal communication) with the subject to reduce the impact of nonspecific therapeutic contact on outcomes. Patients who participate in the study will not be allowed to meet with each other before, during and after assessment or treatments in order to maintain the blind. Patients will be discontinued if they experience worsening in depression, where worsening of depression is defined as an increase in MADRS from baseline of more than 25% during two consecutive assessments, or development of active suicidal intent or attempted suicide.

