## **3.1.6 Interventions**

### *rTMS Treatment Procedures*

Following randomization and baseline MRI, patients will undergo neuronavigation, the target location will be specified by reverse coregistration from a stereotaxic coordinate on the standard Montreal neurological Institute (MNI-152) template brain, on to each individual's anatomical MRI. The MNI coordinates for L and R DLPFC will be [ $\pm 38$  y+44 z+26], drawn from a study identifying this site as optimal based on clinical outcomes and resting-state functional connectivity. rTMS will employ the MagPro X100/R30 stimulator equipped with the B70 fluid-cooled coil for DLPFC stimulation (MagVenture, Farum, Denmark). Neuronavigation will proceed using the *Visor 2* system (Advanced Neuro Therapeutics, Madison, WI) to position the coil for maximal field

[figure not shown]

strength at the left and right target region of the DLPFC for each individual subject. If a participant was unable to complete the MRI they are still able to undergo treatment using beam F3.

Prior to the first treatment, each subject's motor threshold (MT) will first be determined according to published methods during neuronavigated TMS over the primary motor cortex. Subjects will then undergo 20-30 sessions of rTMS, once daily on weekdays for 4 to 6 weeks. One study arm will undergo conventional sequential bilateral rTMS: R DLPFC stimulation at 120% resting motor threshold (RMT) at 1 Hz, in one train of 600 pulses over 10 min, followed by L DLPFC stimulation at 120% of RMT, at 10 Hz, in trains of 4 s with 26 s intertrain interval, for a total of 3000 pulses over 37.5 min. The second study arm will undergo cTBS of the R DLPFC at 120% RMT using bursts of 3 pulses at 50 Hz, bursts repeated at 5 Hz for a total of 600 pulses over 40 seconds, followed by iTBS of the L DLPFC at 120% RMT using bursts of 3 pulses at 50 Hz, bursts repeated at 5 Hz with a duty cycle of 2 s on, 8 s off for a total of 600 pulses over 3 min 9 s. Participants will be titrated to 120% RMT within the first four treatments to aid with tolerability. Subjects who cannot be titrated within 4 days will be allowed to continue in the study but the amount of time to reach the target intensity will be recorded in the treatment logs.

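### Exclusion from the study after more than 3 consecutive missed treatment days leaves randomised participants with no assured MADRS at the week-4/6 endpoint

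*Protocol*

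**What the plan says.** Protocol section 3.1.1 first tolerates absence: "Participants will be permitted to miss scheduled treatment days due to illness or scheduling conflicts". It then sets a limit: "those who miss more than 3 consecutive treatment days will be excluded from the study". Two reasons are given. One is to encourage commitment. The other is to "discourage prolonged duration of time taken to complete the protocol as it could affect the efficacy of the treatment".

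The rule can act only after allocation, because treatment comes later: "Following randomization, patients will undergo a series of clinical and cognitive assessments as well as an MRI (60 minute) and motor threshold testing", and then treatment begins.

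Five other places bear on what happens to an excluded participant:

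- Table 1 has a final-visit column that covers week 4, week 6 or dropout, and the MADRS is marked in it.
- Section 3.2.3 (Outcome Analysis) applies an ANCOVA to the MADRS change at each subject's last time point. It names no analysis population.
- Section 3.1.5 has the clinical scales rated after every 5 sessions and then 1, 4 and 12 weeks after treatment, and allows telephone assessment.
- Section 3.1.4 states that patients and technicians cannot be blinded; raters are.
- Section 3.2.1 raises the sample from 200 to 220 for 10% attrition.

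A related passage in section 3.1.1 concerns participants in remission at weeks 3 and 4, who "will exit the study at week 4 and undergo a post-treatment MRI scan". The same section plans clinical ratings "at 1, 4, and 12 weeks post-treatment".

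**The concern.** A rule that responds to poor attendance may be a reasonable treatment rule. It is a different matter to end observation of a randomised person. Missing several days in a row happens after allocation and may depend on health, mood or the arm itself. If the people it removes have no outcome at the planned endpoint, the groups compared are no longer simply those that randomisation formed.

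Two features make this matter here. Patients know their arm, and the arms differ in the time a session takes. Objective 1 puts it as follows: "To compare the effectiveness of a course of 4 minute sessions of TBS to a course of 45 minute sessions of conventional rTMS". And the design is non-inferiority, where selective loss can push the result either way: towards a false claim for TBS, or towards missing a true one.

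A statistical analysis plan can define analysis sets and handle missing data. It cannot supply MADRS scores that were never taken. That is why the point belongs to the protocol.

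**Working it through.** **1. The plan's own sample size.** Inputs from section 3.2.1: margin 2.75, SD of change 7.8, significance 0.05, power 80%, true difference taken as 0.

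n per arm = 2 × 7.8² × (1.645 + 0.842)² / 2.75² ≈ 99.5, so 100. This matches the stated 100 per arm with a one-sided 0.05 test; one-sided 0.025 would give 127. With 110 randomised per arm and all observed, power is 83.4%. With 10% lost in each arm (99 left), it is 79.8%.

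**2. Session length by arm** (section 3.1.6).

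- Conventional: 10 min on the right, then the left side "for a total of 3000 pulses over 37.5 min", so 10 + 37.5 = 47.5 min.
- TBS: 40 s + 3 min 9 s = 229 s = 3.8 min.
- Ratio: 47.5 / 3.82 ≈ 12. Over 20 sessions this is 15.8 v 1.3 hours; over 30 sessions, 23.8 v 1.9 hours.

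**3. What the protocol assures for an excluded participant.**

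| Source | What it gives |
|---|---|
| Section 3.1.1 | Removal from the study; no later assessment mentioned |
| Table 1 | A dropout visit with MADRS, if exclusion counts as dropout |
| Section 3.1.5 | Ratings counted by sessions attended, so none falls due once sessions stop; follow-up counted from the end of treatment |
| Section 3.2.3 | The last available time point is analysed |

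Reading these together, someone removed in week 2 could enter the ANCOVA with a week-2 score, while others enter at week 4 or 6. The timing of that score is set by attendance. No passage calls for a rating at the planned endpoint.

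**4. Illustration for the worse case, where the excluded leave the analysis.** The documents give no exclusion rates and no outcome gap, so both are assumed. In one arm, with a proportion p excluded:

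retained mean − full mean = p × (retained mean − excluded mean).

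With the same gap in both arms, bias in the treatment difference = (difference in p) × gap. I take gaps from 2.75 (the margin) to 7.8 (one SD), 110 randomised per arm, and 10% excluded on average.

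For 15% v 5%, 93.5 and 104.5 remain, and SE = 7.8 × √(1/93.5 + 1/104.5) = 1.110.

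- Gap 2.75: bias 0.10 × 2.75 = 0.275. Error at the margin if it favours TBS: Φ(−1.645 + 0.275/1.110) = 8.1%. Power if it goes against TBS: Φ((2.75 − 0.275)/1.110 − 1.645) = 72%.
- Gap 7.8: bias 0.10 × 7.8 = 0.78. Error: Φ(−1.645 + 0.78/1.110) = 17.3%. Power: Φ((2.75 − 0.78)/1.110 − 1.645) = 55%.

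| Assumed exclusion | Bias, points | Share of 2.75 | One-sided error if bias favours TBS | Power if bias is against TBS |
|---|---|---|---|---|
| 10% v 10% | 0 | 0% | 5% | 79.8% |
| 12% v 8% | 0.11 to 0.31 | 4% to 11% | 6.1% to 8.6% | 77% to 71% |
| 15% v 5% | 0.28 to 0.78 | 10% to 28% | 8.1% to 17.3% | 72% to 55% |

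**5. The milder case, where exit scores are analysed.** The distortion in each arm is then p × (exit score − unobserved endpoint score). The documents give nothing from which to put a figure on that gap, so the table does not measure this case.

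**The case against.** The strongest reply is that the protocol does not say excluded participants are dropped from the analysis. Table 1 has a dropout visit with the MADRS, ratings are taken every 5 sessions until then, and section 3.2.3 uses each subject's last time point. The natural joint reading is that an excluded person is rated on exit and analysed. The analysis set may also be fixed in a statistical analysis plan that is not at hand.

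This stands, and it rules out several stronger readings:

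- A reader might infer that only completers are compared, or that the as-randomised result is already beyond recovery. The documents establish neither.
- A reader might infer that missed days follow from longer sessions. The protocol names illness and scheduling conflicts, both arms attend once daily on weekdays, and the trigger is a run of consecutive absences. The link to session length is plausible but unproven.
- A reader might take the inflated error rates as an estimate. They rest on assumed inputs, apply only if the excluded leave the analysis, and need a bias towards TBS. If the longer arm lost more people and those people did worse, the bias would run against TBS. The 15% v 5% case also spends the whole 10% attrition allowance on this one rule.

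The reply does not supply an outcome at the planned endpoint. An exit score taken early, at a time set by attendance, is not a week-4 or week-6 score, and no later analysis plan can create one.

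**Conclusion.** The point holds in a limited form. The protocol removes randomised participants from the study on a post-randomisation attendance criterion, in an unblinded non-inferiority trial, and does not provide for rating them at the planned endpoint. The consequence lies between an early exit score standing in for the endpoint and complete loss from the as-randomised comparison. The text does not settle which.

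The size and direction of any bias are unknown. The figure of about 0.3 to 0.8 points (10% to 28% of the margin) is conditional on the excluded leaving the analysis, on exclusion of 15% v 5%, and on a gap of 2.75 to 7.8 points that is equal in both arms. Equal rates with equal gaps give no bias.

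The remitter wording is a secondary inconsistency. Read literally, leaving the study at week 4 takes the best outcomes out of the 1-, 4- and 12-week data. It may mean only the end of treatment, since Table 1 accepts week 4 as a final visit and makes no exception for remitters in follow-up. The primary endpoint is unaffected, because their final MADRS is taken at week 4 either way.

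**What to change.** - In section 3.1.1, replace the wording on exclusion from the study with wording that separates stopping treatment from leaving the study. No view is taken here on how many missed days should be allowed; that treatment rule is for the sponsor.
- State that a participant whose treatment is stopped under the rule keeps the scheduled MADRS ratings through the planned week-4/6 endpoint and the later follow-up, and is analysed in the arm randomised. Because ratings during treatment are counted by sessions, say when the endpoint rating falls for someone no longer attending.
- Reconcile section 3.1.1 with the dropout column of Table 1 and with the last-time-point rule in section 3.2.3, so that it is clear which score enters the ANCOVA.
- Reconcile the week-4 exit of remitters with the planned follow-up, so that they remain in the 1-, 4- and 12-week data.

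Any supportive per-protocol set that uses the missed-days criterion can be left to the statistical analysis plan. The cost is an amendment to wording and a few extra ratings by the existing blinded raters, by telephone where needed, as section 3.1.5 already permits. The change has to come while participants are still being followed, since ratings not taken cannot be recovered.

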### **3.1.2 Subjects**

#### Inclusion Criteria:

Patients will be included if they:

- (1) are an outpatient
- (2) are  $\geq 60$  years old
- (3) have a Mini-International Neuropsychiatric Interview (MINI 6.0) confirmed diagnosis of MDD, with a current MDE
- (4) have failed to achieve a clinical response to an adequate dose of an antidepressant based on an Antidepressant Treatment History Form (ATHF) score of  $\geq 3$  in the current episode or have failed to tolerate two separate trials of an antidepressant
- (5) have a score  $\geq 18$  on the MADRS
- (6) have had no increase or initiation of any psychotropic medication in the 4 weeks prior to screening
- (7) have normal electrolytes, hemoglobin and thyroid functioning based on pre-study blood work
- (8) Pass the TMS adult safety screening (TASS) questionnaire
- (9) Are able to have an MRI

#### Exclusion Criteria:

Patients are excluded if they:

- (1) have a history of substance dependence or abuse within the last 3 months
- (2) have a concomitant major unstable medical illness determined by one of the study physicians
- (3) have active suicidal intent
- (4) have a lifetime MINI diagnosis of bipolar I or II disorder, or primary psychotic disorder
- (5) have current psychotic symptoms
- (6) have a diagnosis of obsessive compulsive disorder, post-traumatic stress disorder (current or within the last year), anxiety disorder (generalized anxiety disorder, social anxiety disorder, panic disorder), or dysthymia, assessed by a study investigator to be primary. One of these comorbidities will not be exclusionary if they are not deemed to be primary.
- (7) have a diagnosis of any personality disorder, and assessed by a study investigator to be primary and causing greater impairment than MDD
- (8) have presumed or probable dementia or clinical evidence of dementia as assessed by a Short Blessed Test score of greater than 10.
- (9) did not respond to a course of ECT in the current depressive episode

[figure not shown]

- (10) have received rTMS in the current episode, patients who have had rTMS in a previous episode would be eligible
- (11) have a history of a primary seizure disorder or a seizure associated with an intracranial lesion.
- (12) have an intracranial implant (e.g., aneurysm clips, shunts, stimulators, cochlear implants, or electrodes) or any other metal object within or near the head, excluding the mouth, that cannot be safely removed
- (13) have a implanted electronic device that is currently function such as a defibrillator
- (14) currently take more than lorazepam 2 mg daily (or equivalent) or any dose of an anticonvulsant
- (15) if participating in psychotherapy, must have been in stable treatment for at least 3 months prior to entry into the study, with no anticipation of change in the frequency of therapeutic sessions, or the therapeutic focus over the duration of the study
- (16) non-correctable clinically significant sensory impairment (i.e., cannot hear well enough to cooperate with interview).

#### Healthy Controls

##### Inclusion Criteria:

Controls will be included if they:

- (1) are  $\geq 60$  years old confirmed with a piece of identification
- (2) have no psychiatric diagnoses as confirmed by the Mini-International Neuropsychiatric Interview (MINI 6.0), except for simple and specific phobias, and past substance abuse or dependence
- (3) have a score  $\leq 10$  on the MADRS
- (4) be on no psychotropic medication
- (5) Are able to have an MRI

##### Exclusion Criteria:

Controls are excluded if they:

- (1) have a history of substance dependence or abuse within the last 3 months
- (2) have a concomitant major unstable medical illness determined by one of the study physicians
- (3) have presumed or probable dementia or clinical evidence of dementia as assessed by a Short Blessed of greater than 10.
- (4) have an intracranial implant (e.g., aneurysm clips, shunts, stimulators, cochlear implants, or electrodes) or any other metal object within or near the head, excluding the mouth, that cannot be safely removed
- (5) have a implanted electronic device that is currently function such as a defibrillator
- (6) non-correctable clinically significant sensory impairment (i.e., cannot hear well enough to cooperate with interview).

### **3.1.3 Recruitment Procedures**

Potential subjects will be recruited from the outpatient geriatric psychiatry clinics at CAMH. They will also be recruited via clinician referrals. Healthy controls will be recruited via newspaper ads, and flyers placed in community clinics and throughout CAMH and surrounding areas.

[figure not shown]

### 3.1.4 Randomization and Blinding

Subjects will be randomized into the study, stratified by severity of treatment resistance (failure > 1 adequate trial). Degree of treatment resistance has been a major predictor of response to treatment in prior rTMS trials and it is essential to ensure that the groups are balanced with respect to this variable. The ATHF is a validated and reliable method of assessing adequacy of prior antidepressant treatment. We will also stratify the randomization by sites to ensure balance in the treatment condition across the two sites. We will randomize subjects based on a stratified randomization scheme using a random permuted block method. As the difference in duration between standard rTMS and TBS protocols is critical to the rationale of the study, it is not possible to blind the rTMS technicians or the patients to treatment assignment; however, since we believe there is equipoise between the two treatments and explain this to patients the expectancy effects should be minimal. **Raters** obtaining outcome measures **will be blind** to treatment assignment. All treatments will be conducted with minimization of personal contact (i.e., verbal communication) with the subject to reduce the impact of nonspecific therapeutic contact on outcomes.

### 3.1.5 Clinical Measures

#### Screening and Baseline evaluation:

Subjects will be screened with the MINI 6.0 to determine eligibility. The MINI assesses current and lifetime depression and other psychiatric disorders. It will be used to clarify psychiatric inclusion and exclusion criteria. The ATHF will be used to confirm eligibility based on inclusion criteria for treatment resistance. The TASS will be used to assess for potential TMS and MRI risk factors. The Short Blessed will be used to screen for dementia at screening. The MoCA will be used to further assess cognition at screening. The Beck Scale for Suicide Ideation (BSS) will be administered to assess for suicidality. A blood test including complete blood count, liver function test and thyroid stimulating hormone will be completed prior to the screening visit in order to rule out any underlying medical causes of the depression. This process is part of the standard of care for all Temerty Centre consultations.

Healthy controls will be screened with the MINI to confirm that they do not meet criteria for current or past psychiatric disorders, except for simple/specific phobias, and past substance abuse or dependence. The TASS will be used to assess safety and eligibility to have an MRI. The Short Blessed will be used to screen for probable dementia at screening. The MADRS and HRDS-17 will be administered to assess for current depressive symptoms. Healthy controls will also complete a urine drug screen (UDS) during their screening appointment to ensure they are not using any illicit substances.

